#### Cost-effectiveness of intervention

The incremental cost-utility ratio will be estimated. It will be obtained by calculating the relationship between the cost of the intervention and the usual care, and its consequences expressed in QALYs.

The cost-utility analysis will refer to the incremental analysis as a result of the quotient between the cost difference of the intervention with respect to usual care, and the change in the results of the difference of cost of the intervention over the difference of cost of the usual care (differences in QALYs). Generalised linear models will be used to model costs and QALYs. Due to the biased distribution of costs, the gamma distribution is usually the most suitable to analyse cost data [73]. The models to estimate differences in costs and QALY will be adjusted for the differences between the two groups in terms of the study covariates. Confidence intervals will be estimated using bootstrap techniques [74] which have the advantage of not having to accept parametric assumptions and whose estimations of standard errors are currently considered very useful and robust in the context of clinical trials [75].

Cost-effectiveness acceptability curves will be obtained based on the theory of net incremental benefit and different hypothetical values of the maximum availability to pay for health gains. These curves represent the probability that an intervention will be more cost-effective than other alternatives and summarise the uncertainty in cost-effectiveness analysis.

Simple sensitivity analyses will be performed. One or more parameters of the evaluation that generate uncertainty will vary in order to see how they affect the robustness of the results. We will conduct a complete case analysis, analysis changing the unit cost of services, andan analysis using the average wage instead of the minimum wage. If the results are sensitive to their variations, simultaneous sensitivity analyses will be performed adjusting for all the sensitive parameters by multiple regression methods.

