### Sample size

The sample size was calculated on the basis of data from the literature and some results of phase II. We expect a difference in the percentage of people who show a positive change in one or more of the three behaviours between the two groups of at least 8%. Assuming 30% patient loss to follow-up, alpha risk of 5%, beta risk of 20%, and an intracluster correlation of 0.01 [68], we consider that it is necessary to study a minimum of 140 participants for each PHC centre, a total of 3640 people (1820 for each of the two groups, 13 PHC centre per group). PASS software was used to compute the sample size [PASS 14 Power Analysis and Sample Size Software (2016). NCSS, LLC. Kaysville, Utah, USA, ncss.com/software/pass]. Sampling was done in order to fulfil an established sex and age quota which is proportional to the last general population census.

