### Assignment of intervention

The allocation schedule for random assignment of intervention to PHC centres will be computer generated at a central location (IDIAP Jordi Gol, Barcelona, Spain). For each of the seven Spanish Autonomous Communities, we will randomly allocate half of the PHC centres to the intervention group and the other half to the control group. In total, 13 PHC centres will be allocated to the intervention group and 13 other to the control group. The allocation will not be concealed at PHC centres and no blinding will be done.

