### Analysis

#### Effectiveness of intervention

All analyses will be carried out in accordance with the intention-to-treat principle. Depending on the characteristics of the variables, it will be assessed if it is appropriate to make multiple imputationin the variables with missing data or to make a conservative approach to data loss. Multiple imputation will be the preferred technique for dealing with missing data, and the conservative approach will be used when the data indicate that it is the most appropriate. Multiple imputation by chaining equations procedure will be used to obtain at least 20 imputed datasets and Rubin’s rules will be used to combine them [72]. Sensitivity analyses will be performed for the primary and secondary outcomes to assess the impact of the multiple imputation or the conservative approach to data loss.

Descriptive and bivariate analyses will be calculated for all variables of interest. We will use cluster specific methods because PHC centres will be randomised. In order to analyse the effect of the intervention on each outcome measure, we will use hierarchical linear or logistic regressions models for clustered data. We will also analyse the variables associated with the change in the adherence to the Mediterranean diet, physical activity level and smoking cessation adjusting for possible confounding variables. Final models will be chosen coherently with the study objectives and the nature of the variables (potential confounders, significant and clinically relevant variables). The interactions and collinearity of the models will be evaluated. The size of the effect (Cohen’s d) will also be calculatedand the number needed to treat will also be calculated..

The level of significance of the models will be set at 5%. Stata/SE v.15 or higher (StataCorp, LP, TX) and R version 3.4.4 or higher will be used for statistical analysis.

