#### Effectivenessof implementation strategy

The assessment of the implementation strategy will be carried out through qualitative and quantitative methodologies. We will evaluate it in terms of:Implementation outcomes (stated earlier).Determinants.Characteristics of PHC centres and professionals will be analysed as determinants of implementation. Furthermore, three focus groups (one of the health professionals and two of participants) will be conducted in each PHC centre in the post-implementation stage. Sampling will be theoretical (discursive plurality). Sessions will be transcribed in an anonymous way. A thematic content analysis will be done and data will be coded in accordance with CFIR constructs [76]. Moreover, these results will be analysed quantitatively. CFIR constructs will be scored following standard criteria that will reflect the influence of the construct on the implementation (positive or negative) and its magnitude (between 1 and 2) [77].*Level of development*. The level of development of each of the implementation strategies will be determined from an online database. Updating of this database will be carried out by the implementation facilitator. Likewise, we will develop logistic regression models in which the dependent variable will be the effectiveness of the intervention, considered as a positive change in any of the three behaviours studied. The independent variables will be the quantitative measures of the results of the implementation and the degree of implementation of the different strategies. The purpose of these analyses is to model the relationship between the implementation variables and those of effectiveness. On the other hand, the influence and the magnitude of the determinants of the implementation and the results will be established through multivariate models.

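### The cost-utility and implementation analyses name methods with no allowance for centre, although the effectiveness analysis requires one; run as written, their intervals would be too narrow

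*Protocol article*

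**What the plan says.** - **Randomisation** (*Assignment of intervention*): "In total, 13 PHC centres will be allocated to the intervention group and 13 other to the control group". Centres are split half and half within each of seven Autonomous Communities.
- **Sample size**: "Assuming 30% patient loss to follow-up, alpha risk of 5%, beta risk of 20%, and an intracluster correlation of 0.01", leading to 140 participants per centre, 1820 per arm and 3640 in all. The target is a difference of 8 percentage points in the proportion improving on at least one behaviour.
- **Effectiveness of intervention**: "We will use cluster specific methods because PHC centres will be randomised". The section then specifies multilevel linear or logistic models for the intervention effect on each outcome measure.
- **Cost-effectiveness of intervention**: "Generalised linear models will be used to model costs and QALYs". A gamma distribution is suggested for costs, the models are adjusted for study covariates, and "Confidence intervals will be estimated using bootstrap techniques". No centre effect, cluster-robust variance or resampling unit is given.
- **Effectiveness of implementation strategy**: "we will develop logistic regression models in which the dependent variable will be the effectiveness of the intervention". The predictors are the measured implementation results and how far each strategy was put into practice. Centre is not mentioned here either.
- **Study objectives**: cost-effectiveness is part of the first primary objective.

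**The concern.** The trial is randomised by centre, its size allows for that, and one of its three analysis sections acts on it. The other two name their own methods, and the model sentence in the effectiveness section does not clearly reach them. A gamma model for costs is neither linear nor logistic. The implementation regression does not estimate the intervention effect; it relates implementation variables to behaviour change.

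The bootstrap does not solve this by itself. The article justifies it by its freedom from parametric assumptions, but a bootstrap that resamples participants still assumes that they are independent.

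At stake on the economic side are the intervals for incremental cost, incremental QALYs and their ratio, and the acceptability curve, which is itself a statement of uncertainty. In the implementation regression, a predictor shared by everyone in a centre is tested as if about 98 people per centre each brought separate information on it. Associations with such predictors would then appear by chance too often.

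**Working it through.** **Inputs from the article.** 13 centres per arm, 140 participants per centre, 30% loss, ICC 0.01, 5% alpha, 80% power, 8-point difference. **Assumptions.** Two-sided alpha; the control proportion (not stated); ICCs for costs and QALYs (not stated).

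**1. The plan's own sample size.** Analysed per centre: m = 140 × 0.70 = 98. Design effect: DEFF = 1 + (m − 1) × ICC = 1 + 97 × 0.01 = 1.97. For 46% against 54%, the least favourable pair, two independent proportions need 613 per arm, or 637 with continuity correction. Inflating for clustering and loss:
- 613 × 1.97 / 0.70 gives 1726 per arm.
- 637 × 1.97 / 0.70 gives 1793 per arm.

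Both round up to 13 centres per arm (637 × 1.97 / 98 = 12.8). The stated 1820 is therefore compatible with a design effect near 2, so the plan already accepts that centre matters.

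**2. Ignoring centre in an arm comparison.** The standard error is too small by √DEFF. True coverage of a nominal 95% interval is 2Φ(1.96/√DEFF) − 1.

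| ICC | DEFF | √DEFF | Coverage | True size of a 5% test |
|---|---|---|---|---|
| 0.005 (assumed) | 1.485 | 1.22 | 89% | 11% |
| 0.01 (plan, behaviour outcome) | 1.97 | 1.40 | 84% | 16% |
| 0.02 (assumed) | 2.94 | 1.71 | 75% | 25% |
| 0.05 (assumed) | 5.85 | 2.42 | 58% | 42% |

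At ICC 0.01 the naive interval has 1/1.40 = 0.71 of the correct width. The 26 × 98 = 2548 analysed participants carry the information of about 2548/1.97 = 1293 independent ones.

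**3. Acceptability curve.** If the correct probability of being cost-effective is 0.80 (z = 0.84) and the standard error of net benefit is understated by 1.40, the curve would show Φ(0.84 × 1.40) ≈ 0.88. At an assumed ICC of 0.05 it would show about 0.98.

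**4. Implementation regression.** Null centre-level predictors were simulated: beta-binomial outcomes, 98 per centre, 30% improving (assumed), 4000 runs, ordinary logistic regression tested at 5%. The article does not say which centres enter, so both numbers were tried.

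| Centres | ICC | Ordinary logistic rejects | Centre-level regression rejects |
|---|---|---|---|
| 13 | 0.01 | 15.9% | 4.5% |
| 26 | 0.01 | 16.1% | 5.1% |
| 13 | 0.05 | 41.1% | 5.0% |
| 26 | 0.05 | 40.5% | 4.4% |

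These rates apply to predictors that are constant within a centre. For a predictor with its own within-centre correlation r, the variance inflation is roughly 1 + 97 × r × ICC. That is 1.97 at r = 1 and 1 at r = 0 for ICC 0.01, so predictors that vary by participant are less affected.

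**The case against.** The strongest reply is that silence is not a decision. A generalised linear model can carry a centre effect or cluster-robust variance, and a bootstrap can resample centres. The reason given in the effectiveness section, that centres are randomised, is general, and its reference to each outcome measure could be stretched to costs. A journal article may also leave such detail to a fuller plan. This stands in part: a reader might infer that the plan has chosen to drop clustering, and the text does not support that. But the cost-utility section is not merely brief. It fixes the model class, the likely distribution, the adjustment, the interval method and the sensitivity analyses, and none of these deals with centre.

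Other strong readings also fail:
- **Costs and QALYs modelled separately.** The article does not say so, and a participant bootstrap would keep each pair together.
- **Mostly centre-level predictors, all in one joint model.** A reader could count seven implementation outcomes and 11 strategy rows in Table 3 against 13 intervention centres. But the article speaks of models in the plural and specifies no joint fit. Some measures come from individual professionals or participants, such as the surveys and the activities recorded in the case report form.
- **About 70% chance of a false finding across seven predictors.** 1 − 0.84^7 gives that figure, but only if all seven are independent, constant within centre and tested one by one. It also mixes in multiplicity: 1 − 0.95^7 is 30% with no clustering at all.
- **A failed primary implementation objective.** That objective concerns acceptability, adoption, fidelity and the like. The regression has a separate stated purpose.

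**Conclusion.** The point holds as an inconsistency within the article with a conditional consequence. One section requires cluster methods, and two others name methods without them. If those two are run as written with participants treated as independent, standard errors are too small by a factor of 1.40 and 95% intervals cover about 84%, given 98 analysed per centre and an ICC of 0.01. That ICC was stated for the behaviour outcome; for costs and QALYs it is an assumption, and coverage runs from about 89% at 0.005 to about 58% at 0.05. In the implementation regression, a null predictor that is constant within a centre is rejected about 16% of the time at ICC 0.01. The economic part matters more, because cost-effectiveness belongs to a primary objective.

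**What to change.** **Cost-effectiveness of intervention.** State one of two routes:
- The cost and QALY models include a centre effect, for example a bivariate multilevel model.
- The bootstrap resamples whole centres within arm and keeps each participant's cost and QALY together. Autonomous Community can enter as a covariate if wanted.

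The resampling should not be done within arm and Autonomous Community. Two centres in each of seven Communities would need 14 per arm and there are 13, so at least one stratum holds one centre or none. A one-centre stratum contributes no between-centre variance, and a two-centre stratum contributes about half (1 − 1/2). Resampling 13 centres within arm loses far less: the factor is 1 − 1/13 on the variance, or √(12/13) = 0.96 on the standard error.

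**Effectiveness of implementation strategy.** State that the logistic models include a centre random intercept and that centre-level predictors are tested against a small-sample reference distribution. If only the 13 intervention centres enter with one such predictor, that means about 13 − 2 = 11 degrees of freedom. Enter only one or two centre-level predictors at a time and label the results exploratory.

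**Cost.** A few sentences and little code, with no new data. Intervals will be wider (by about 1.40 at ICC 0.01), and fewer centre-level predictors can be studied in one model.

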Beginning or making a behaviour change. The proportion of people who are in the stages of action, maintenance or termination according to the TTM at the study entry and at 12 months.Change from baseline on sedentary behaviour. It will be measured by the sitting items from the International Physical Activity Questionnaire.Change from baseline on diet quality. Diet Quality Index-International will be used to determine diet quality [52].Change from baseline on health-related quality of life. It will be measured by the EuroQol-5D questionnaire [53].Reduction of the cardiovascular risk. The proportion of people with low/moderate and high/very high baseline cardiovascular risk who have reduced it. Cardiovascular risk will be calculated using REGICOR [54, 55] and SCORE [56] function charts.Change from baseline on body mass index. Body mass index is defined as the body weight divided by the square of the body height and is expressed in units of kg/m^2^.Change from baseline on waist circumference. The waist circumference will be measured at a level midway between the lowest rib and the iliac crest. It will be expressed in units of cm.Change from baseline on blood pressure. It will be measured in the routine clinical practice by validated electronic monitors and it will be expressed in units of mmHg.Change from baseline on lipid profile. The lipid profile will include: low-density lipoprotein, high-density lipoprotein, triglycerides and total cholesterol. They will be expressed in units of mg/dl.Change from baseline on arterial stiffness. Arterial stiffness will be assessed by the “Cardio-Ankle Vascular Index”. It will be measured by the Vascular Screening System VaSera VS-1500 N or VaSera VS-2000.Change from baseline on theankle-brachial index. It will be measured by the Vascular Screening System VaSera VS-1500 N or VaSera VS-2000.Change from baseline on the “REgicor and Artper Score fOr aNkle brachial index (REASON)” [57].Change from baseline on the perceived functional social support. The questionnaire Duke-UNC-11 will be used to determine the perceived functional social support [58–60].Reduction of the incidence of major depression will be evaluated by CIDI interview [61].Reduction of the risk of depression in participant non-depressed at baseline. Risk of depression will be calculated using the algorithm PredictD [62].Reduction of depression symptoms. The Patient Health Questionnaire-9 will be used to determine the prevalence and the severity of depression symptoms [63].Reduction of anxiety symptoms. The General Anxiety Disorder-7 questionnaire will be used to determine the prevalence and the severity of anxiety symptoms [64].Change from baseline on unhealthy behaviours of professionals of the PHC intervention centres.

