
#### ii) Cost-effectiveness outcomes

An economic evaluation will be conducted from the perspective of the society and the Health Service comparing the EIRA intervention vs. the usual care group at 12-months post-intervention.
*Outcome measure*
Incremental cost per quality-adjusted life years (QALYs) gained will be calculated. QALYs will be measured using the Spanish tariffs of the EuroQol-5D questionnaire [53]. The following costs will be taken into account: hospital care (emergency visits and stays), secondary care (visits to specialists), primary care (visits to physician and nurse), social care services (visits to social worker), outpatient diagnostic tests, medication use, group sessions attended, community resources used and loss of productivity (days off work). This information will refer to the last 12 months prior to study entry and to the subsequent 12 months. Use of healthcare resources and lost productivity will be assessed through the patients’ clinical history and also the Client Service Receipt Inventory [65]. Information on the use of medicines (active substance, dose, and units supplied) will also be collected. The unit costs of public healthcare services will be obtained from the Official Bulletin of the Government. Costs of privately funded services will be obtained from published tariffs. The mean price per milligram of active substance will be calculated using the prices of the generic versions of all the presentations as reported in the Spanish Vademecum. Productivity losses will be calculated based using information on the minimum and average daily wage in Spain [66].

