### Data collection and management

Data will be collected at PHC centre, professional and participant levels. Data collection methods and procedures are summarised in Table 4.

**Table 4 Tab4:** Schedule of Data Collection Methods and Procedures

			Pre-implementation/Pre-study consent/screening	During implementation			Post-implementation
Activity/Assessment	Data collection	Responsible		Study baseline	Intervention visits	Follow-up 12-months	
PHC centre level							
Characteristics of assigned people	Form report	Research team each autonomous community	x				
Organisational structure	Form report	Research team each autonomous community	x				
Survey of Organizational Attributes for Primary Care	Self-administered questionnaire	Research team each autonomous community	x				x
Professional level							
Age, sex, academic education and experience in PHC	Self-administered questionnaire	Research team each autonomous community	x				
Daily consumption of fruits and vegetables/Level of physical activity/Smoking behaviour	Self-administered questionnaire	Research team each autonomous community	x				x
Appropriateness and acceptability	Self-administered questionnaire	Research team each autonomous community	x				x
Determinants of implementation (CFIR constructs)	Focus group	Research team each autonomous community					x
Participant level							
Informed consent	Paper document	PHC professionals	x				
Age and sex	CRF	PHC professionals	x				
Screening unhealthy behaviours	CRF	PHC professionals	x				
Inclusion/Exclusion criteria	CRF	PHC professionals	x				
Adherence to the Mediterranean dietary pattern	CRF (14-item Questionnaire of Mediterranean diet adherence	External unit of local trained personnel		x		x	
Quality of diet	CRF (Diet Quality Index-International)	External unit of local trained personnel		x		x	
Physical activity behaviour	CRF (International Physical Questionnaire)	External unit of local trained personnel		x		x	
Smoking behaviour	CRF (interview and optional cooximetry)	External unit of local trained personnel		x		x	
Stage of change	CRF	PHC professionals (intervention group)		x		x	
		External unit of local trained personnel (control group)		x		x	
Health-related quality of life	CRF (EuroQol-5D questionnaire)	External unit of local trained personnel		x		x	

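### Adjustment of the cost and QALY models is tied to between-arm differences in an undefined covariate set, with no commitment to baseline EQ-5D utility or prior-year cost

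*Protocol article*

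**What the plan says.** All references are to the protocol article.

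- **Cost-effectiveness of intervention (Analysis).** On model type: "Generalised linear models will be used to model costs and QALYs". On covariates, the models "will be adjusted for the differences between the two groups in terms of the study covariates". The section lists no covariates, does not define the study covariates, and gives no criterion for what counts as a difference. Confidence intervals come from a bootstrap whose resampling unit is not stated.
- **Cost-effectiveness outcomes.** "QALYs will be measured using the Spanish tariffs of the EuroQol-5D questionnaire". On resource use: "This information will refer to the last 12 months prior to study entry and to the subsequent 12 months".
- **Data collection and management, Table 4.** EQ-5D and 12-month resource use are recorded at baseline and at the 12-month follow-up, the only two visits made by the external data-collection unit.
- **Effectiveness of intervention (Analysis).** "We will use cluster specific methods because PHC centres will be randomised". The cost-effectiveness section has no equivalent statement.
- **Study objectives and hypotheses.** Cost-effectiveness is part of the first primary objective.

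**The concern.** In a randomised trial, covariates earn their place by how strongly they predict the outcome, and they are best named before the data are seen. Choosing them by observed imbalance reverses this. A strong predictor that happens to look balanced is left out, and its precision gain goes with it. A moderate imbalance that nobody calls a difference stays in the estimate.

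This matters more for QALYs than for most outcomes. With utility measured only at baseline and 12 months, an area-under-curve QALY is the average of the two values, so half of the outcome is the baseline value itself. Prior-year cost is likewise the obvious predictor of cost in the following year. At stake are the width of the intervals for incremental QALYs and costs, the shape of the acceptability curves, and how much of both rests on the analyst's view of what differs.

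**Working it through.** **The plan's own figure.** The article states no figure for the QALY or cost analysis. Its sample size (13 centres × 140 = 1820 per arm, 3640 in total) concerns behaviour change. The control rate is not given. With an assumed 46% v 54% and continuity correction, 637 × 1.97 / 0.70 ≈ 1793, which is close to 1820. That figure has no bearing on this point beyond supplying cluster numbers.

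**Inputs from the article (Sample size).** 13 centres per arm, 140 per centre, 30% loss and intracluster correlation (ICC) 0.01. Evaluable participants: 140 × 0.70 = 98 per centre and 13 × 98 = 1274 per arm. The ICC was set for the behaviour outcome and is borrowed here.

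**Assumptions (not in the article).** QALY = (u0 + u12)/2 over one year; utility SD 0.20 at both times (range 0.15–0.25); correlation rho = 0.6 between u0 and u12 (range 0.4–0.8), the same within and between centres; the same ICC at both times.

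**Step 1: chance imbalance in baseline utility.**
- Design effect = 1 + 97 × 0.01 = 1.97; effective n = 1274/1.97 ≈ 647 per arm.
- SE of the baseline difference = 0.20 × √(2/647) = 0.0111.
- 1.96 × 0.0111 = 0.022.

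**Step 2: carry-over.** Without adjustment, a baseline imbalance d shifts the QALY difference by d(1 + rho)/2. At rho 0.6 this is 0.8d. An imbalance of 0.022, just short of p<0.05, therefore leaves about 0.017 QALY in the estimate. Over SD 0.15–0.25 and rho 0.4–0.8 at ICC 0.01, the figure is 0.011 to 0.025.

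**Step 3: precision if baseline utility is never or always in the model.**
- Never: SE = 0.0111 × √((1 + rho)/2) = 0.0111 × 0.894 ≈ 0.0100.
- Always: SE = 0.0111 × √((1 − rho²)/4) = 0.0111 × 0.40 ≈ 0.0044.
- Variance ratio = (1 − rho)/2, which is 0.30, 0.20 and 0.10 at rho 0.4, 0.6 and 0.8.

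**Step 4: precision if it enters only when imbalanced.** The article gives no trigger, so p<0.05 is assumed for illustration. Under that rule, adjustment happens in 5% of trials. In the other 95% the imbalance stays in. The share of imbalance variance that remains is 0.95 − 2 × 1.96 × 0.0584 = 0.72, where 0.0584 is the normal density at 1.96. At rho 0.6:
- Variance = 0.00445² + 0.8² × 0.01112² × 0.72 ≈ 0.0000198 + 0.0000570 = 0.0000768.
- SE ≈ 0.0088. A 200,000-draw simulation gives the same value.
- About 72% of the variance reduction available from always adjusting is lost.

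| rho | never | only if p<0.05 | always |
|---|---|---|---|
| 0.4 | 0.0093 | 0.0083 | 0.0051 |
| 0.6 | 0.0100 | 0.0088 | 0.0044 |
| 0.8 | 0.0105 | 0.0091 | 0.0033 |

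At ICC 0.03 (SD 0.20, rho 0.6) the never and always values rise to 0.0140 and 0.0063. The ratio is unchanged.

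**Step 5: costs.** On a linear scale, always including prior-year cost leaves 1 − r² of the variance: 91%, 75% or 51% at assumed correlations r of 0.3, 0.5 or 0.7.

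**The case against.** The strongest reply is that the article neither names nor excludes the two variables. Both are collected at baseline, and prior-year resource use is specified within the economic outcomes themselves, so both are natural members of the study covariates. The sentence may be loose English for ordinary covariate adjustment: it contains no test or threshold, and the surrounding paragraph is awkwardly worded elsewhere. A condensed article may also leave its covariate list to a fuller plan.

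Much of this stands. A reader might infer that the plan adjusts for imbalanced covariates *in place of* baseline utility and prior-year cost. The text does not support that. Nor does it show that the QALY analysis will be unadjusted, so the comparison of 0.0100 with 0.0044 is an outer bound and not a description of the plan. The p<0.05 trigger is an illustration. If EQ-5D counts as a study covariate, a marked imbalance would bring it into the model, and only imbalance short of that passes through.

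A reader might also infer systematic bias or false positives. Randomisation makes chance imbalance an error conditional on the allocation that occurred, not a bias. Under the assumed trigger with model-based standard errors, the simulated type I error was about 2.3% at rho 0.6, which is conservative. Allocation is not concealed at the centres, but the article does not say whether centres know their arm while recruiting, so systematic baseline differences cannot be claimed from it.

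What does not stand is that this is only a missing list. The sentence states a basis for adjustment, differences between the groups, and that basis is a poor one. Even on the kinder reading the covariate set is undefined, and the same rewording cures it.

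On clustering, the effectiveness section gives a trial-wide reason for cluster methods and applies hierarchical models to each outcome measure, so a reader should not conclude that clustering will be ignored in the economic analysis. It is only unstated there.

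**Conclusion.** The point holds as one about pre-specification and precision. The stated criterion points to observed imbalance in an undefined set and makes no commitment to the two baseline variables that matter most. If baseline utility enters only when it looks different, the standard error of the QALY difference is about twice what it need be (0.0088 against 0.0044), and up to about 0.017 QALY of undeclared imbalance can remain in the estimate. These sizes rest on the area-under-curve formula, the assumed SD, ICC and rho, and the assumed trigger. The variance ratio of always to never adjusting, 0.30 to 0.10 over rho 0.4–0.8, does not depend on SD or ICC. The gain for costs is smaller and depends on a correlation that the article does not give. The clustering of the economic models is a secondary point, and the conclusion does not depend on it.

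**What to change.** Replace the adjustment sentence in the cost-effectiveness analysis section with:

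> The QALY model will include baseline EQ-5D utility and the cost model will include cost in the 12 months before entry (in a form suited to the link function), together with Autonomous Community, whatever the observed baseline differences.

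The note on form is needed because gamma models are favoured for costs. Under a log link, skewed and untransformed prior-year cost can be highly influential. Autonomous Community belongs in the models because centres are randomised within it.

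As a secondary change, state that the economic models allow for clustering by centre and that the bootstrap resamples centres within arm, respecting the Autonomous Community strata where numbers allow. The qualifier matters: 13 centres per arm over seven Communities means that, with equal halves, at least one Community has a single centre per arm (7 × 2 = 14 > 13).

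The cost is wording only. Both baseline variables are already collected, so no new data, visits or participants are needed. The one piece of work is to choose the form of prior-year cost before the data are seen.
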